#### Secondary outcomes

1: Time to Local Progression (TLP). ‘Target liver volume’ will be determined with the use of cone-beam CT during the interventional procedure, by implementing the perfusion area of the targeted vessel in relationship to the anatomic localization of the liver lesion(s). TLP will be defined as the time elapsed since the start of treatment (baseline is the date of minimization) until *local* tumor progression, ‘local’ indicating a constriction to the target liver volume as defined by cone-beam CT. Local tumor progression will be based on the mRECIST criteria and defined as: An increase of at least 20% in the sum of the diameters of viable (enhancing) target lesions (whereas target lesions for TLP evaluation are only considered within the ‘target liver volume’), taking as a reference the smallest sum of the diameters of viable (enhancing) target lesions recorded since treatment started, and/or unequivocal progression of existing no target lesions within this perfusion area and/or the appearance of one or more new (enhancing) lesions within this perfusion area; 2: Overall survival; 3: Overall response to therapy according to mRECIST; 4: Toxicities and adverse events; 5: Quality of life; 6: Treatment-related costs, in terms of cost of therapy and number of hospitalization days, in these patients. Cost-effectiveness of ^90^Y-RE versus TACE will be assessed.

#### Sample size calculation

A total of 140 patients will be included. Sample size calculation was performed using PASS (Power Analysis and Sample Size software, NCSS, Kaysville, Utah, USA), using the log rank test. Assuming a follow-up time of 24 months and a median time to progression of 13.3 months after ^90^Y-RE, based on the best stratified data for intermediate stage HCC patients available in the literature [25], a clinically relevant effect size of 20% difference in time to progression (2.7 months) with a power of 90% and a two-sided Alpha Risk of 5%, 70 patients in each treatment arm will be required. Taking a hypothetical loss to follow-up of 2% into account in both treatment arms, based on earlier experience with this patient group, still gives a power of 80% if 70 patients per treatment arm are included (Alpha Risk remains 5%).

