#### Null hypothesis

There is no difference in TTP in patients with intermediate stage HCC treated with ^90^Y-RE or TACE-DEB.

The alternative hypothesis is two-sided (^90^Y-RE could have a shorter or a longer TTP).

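### With 70 patients per arm, the stated inputs give about 21% power (15% if TACE is the longer arm) for a 2.7-month difference in TTP, not the stated 90% or 80%

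*Protocol article*

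**What the plan says.** The Protocol article's section on sample size calculation gives a full set of inputs and a result.

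- Size: "A total of 140 patients will be included", and "70 patients in each treatment arm will be required".
- Method: PASS software, "using the log rank test".
- Reference arm: "Assuming a follow-up time of 24 months and a median time to progression of 13.3 months after ^90^Y-RE".
- Effect and power: "a clinically relevant effect size of 20% difference in time to progression (2.7 months) with a power of 90" per cent.
- Error rate: "a two-sided Alpha Risk of 5" per cent.
- Attrition: "Taking a hypothetical loss to follow-up of 2% into account in both treatment arms", after which 70 per arm is said still to give 80% power.

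The section gives no hazard ratio, number of events or accrual pattern. The section on the null hypothesis makes the alternative two-sided, so TTP after radioembolization may be shorter or longer than after TACE. The section on statistical analyses plans a log-rank test for the primary outcome and a hazard ratio (HR) with its 95% confidence interval.

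**The concern.** A 20% difference between medians near 13 months is a modest effect, with an HR of about 0.80. Detecting it with 90% power normally takes several hundred events, and this trial has 140 patients in all. The two power statements also sit oddly together: losing 2% of patients should hardly change power, yet the text has it fall by ten percentage points.

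This paragraph is the only justification for the sample size on the primary outcome. If the claim is wrong, the trial is presented as very likely to detect a 2.7-month difference that it would in fact miss about four times in five. There is then a risk that a non-significant result is taken as good evidence of similar TTP, particularly as the study rationale cites retrospective comparisons that found the two treatments similar.

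**Working it through.** **Inputs from the sample size section:** 70 per arm; reference median 13.3 months; difference 20% × 13.3 = 2.66, rounded to 2.7 months; follow-up 24 months; two-sided alpha 5% (z = 1.96); log-rank test. The other median is therefore 10.6 or 16.0 months.

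**Assumptions added here:** exponential TTP, and a full 24 months of follow-up for every patient.

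**Convention:** each HR is for the longer-median arm relative to the shorter-median arm.

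**Step 1: expected progressions.** P(progression by 24 months) = 1 − 2^(−24/median).

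- Median 13.3: 0.714
- Median 10.6: 0.792
- Median 16.0: 0.646

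Events for 13.3 v 10.6: 70 × (0.714 + 0.792) ≈ 105.
Events for 13.3 v 16.0: 70 × (0.714 + 0.646) ≈ 95.

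**Step 2: power (Schoenfeld).** Power = Φ(|ln HR| × √events / 2 − 1.96).

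| Medians | HR | \|ln HR\| | Events | Power | Power if all 140 progress |
|---|---|---|---|---|---|
| 13.3 v 10.6 | 0.797 | 0.227 | 105.4 | Φ(1.165 − 1.96) = 21% | 27% |
| 13.3 v 16.0 | 0.831 | 0.185 | 95.2 | Φ(0.902 − 1.96) = 15% (14.5%) | 19% |

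Freedman's form gives 21.2% and 14.4%. A log-rank simulation with 20,000 runs per scenario gives 21.2% and 15.0%. The stated 90% is not reproduced. One-sided testing would give only 32% and 23%.

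**Step 3: events needed for 90% power.** Events = 4 × (1.96 + 1.2816)² / (ln HR)².

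- 13.3 v 10.6: 42.03 / 0.0515 ≈ 816 events. Divided by the mean event probability of 0.753, this is about 1,085 patients.
- 13.3 v 16.0: 42.03 / 0.0342 ≈ 1,230 events, or about 1,810 patients at a mean event probability of 0.680.

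**Step 4: what 70 per arm can detect.** The Step 2 formula is solved for the TACE median, with the event count recalculated for each value.

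| Power | TACE median | Difference from 13.3 | HR | Expected events |
|---|---|---|---|---|
| 90% | 7.2 months | 6.1 shorter | 0.54 | 113 |
| 90% | 27.2 months | 13.9 longer | 0.49 | 82 |
| 80% | 7.8 months | 5.5 shorter | 0.59 | 112 |
| 80% | 24.5 months | 11.2 longer | 0.54 | 85 |

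The expected event count depends on the scenario, so 105 belongs to 13.3 v 10.6 months only and is not a maximum.

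**Step 5: the 80% claim.** Suppose power really were 90%. With 2% fewer events it becomes Φ(3.2415 × √0.98 − 1.96) = Φ(1.249) ≈ 89.4%. A fall to 80% needs the event count to shrink by the factor (1.96 + 0.8416)² / (1.96 + 1.2816)² = 7.849 / 10.507 ≈ 0.75, which is about 25% fewer events. For the effect actually stated (13.3 v 10.6 months), a 2% loss leaves power at about 21%.

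**Step 6: precision.** With 105 events the 95% confidence interval spans a factor of exp(1.96 × 2/√105.4) ≈ 1.46 on either side of the estimate. An estimate of 0.797 would run from about 0.54 to 1.17.

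**The case against.** **The exponential model and complete follow-up are not in the document.** That is true, but they do not drive the result. With every one of the 140 patients progressing, power for 13.3 v 10.6 months is still 27%.

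**The 20% may have been entered as percentage points progression-free.** This is the strongest alternative. At 24 months the 13.3-month median leaves about 29% progression-free. Taking 29% v 9%, 70 per arm gives 93% to 95% power (Freedman, Schoenfeld); taking 29% v 49%, it gives 70% to 72%. If the 2% loss is also read as 2% per month, a time unit that the text does not give, 29% v 9% comes to about 89% to 91%. So the software may have received a different effect, which is a reason to check its inputs. It does not rescue the paragraph: the text converts the effect to 2.7 months, and it attaches 80%, not 90%, to the case with loss.

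**An article condenses the full protocol.** This would excuse a missing detail. Here the inputs and the result are both printed, and they disagree.

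**A stronger reading is tempting.** A reader might infer that the plan intends to treat a non-significant result as showing equal TTP, or that the null hypothesis, "There is no difference in TTP in patients with intermediate stage HCC", is itself a mistake. The document supports neither. That null is the standard one for a two-sided test, nothing in the plan claims equivalence, and the analysis section already provides the HR and its interval. Misreading is a risk created by the power claim, not something that the plan proposes.

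**Conclusion.** The point holds. On the inputs as printed, the two-sided 5% log-rank test with 70 per arm has about 21% power if the TACE median is 2.7 months shorter and about 15% if it is 2.7 months longer. Both the 90% and the 80% statements are wrong for that difference, and they do not fit each other. The exact percentages rest on exponential TTP and full 24-month follow-up; the conclusion does not, given the ceiling with all 140 events. Deaths before progression would reduce the number of progressions, which lowers power, enlarges the detectable difference and widens the confidence interval. What cannot be told from the document is whether the calculation itself failed or a different effect was entered and then misdescribed.

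**What to change.** 1. Check the inputs given to the software. If a different effect was entered, correct the stated effect so that it matches the calculation.
2. Otherwise keep 140 patients and delete both the 90% and the 80% power claims for 2.7 months. State instead about 21% power (TACE median 10.6 months, about 105 expected progressions) or about 15% (TACE median 16.0 months, about 95).
3. State the detectable difference in both directions, since the alternative is two-sided: 90% power for a TACE median of about 7.2 or 27.2 months, and 80% power for about 7.8 or 24.5 months, with the HRs tabulated above. Give the assumptions, and note the effect of deaths before progression.
4. Add one sentence saying that a non-significant log-rank test will not be read as equal TTP and will be interpreted through the HR and 95% confidence interval already planned.

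The cost is protocol wording only; treatment, visits and the planned analysis do not change. The downside is that the stated power becomes much less favourable. The trial status section reports only the first 10 patients allocated and treated, with results pending, so the correction can be made before results are known.

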### Yttrium-90 radioembolization

Yttrium-90 radioembolization (^90^Y-RE) is a relatively recently developed technique which involves the transarterial administration of minimally embolic microspheres loaded with Yttrium-90, a β-emitting isotope, delivering selective internal radiation to the tumor. This brachytherapy device is approved by the Food and Drug Administration for HCC with and without portal vein thrombosis (PVT). Several prospective and retrospective studies demonstrated the safety and efficacy of 90Y-RE treatment for unresectable HCC, all documented in a recent review [23]. An earlier structured meta-analysis describes a response rate of 78% (glass microspheres) and 89% (resin microspheres) [24]. The largest prospective study to date included 291 HCC patients that were treated with ^90^Y-RE [25]. In intermediate stage patients (BCLC stage B) median time to progression was 13.3 months (Child-Pugh A, 13.3 months and Child-Pugh B, 17.4 months) and median survival was 17.2 months (Child-Pugh A, 17.3 months and Child-Pugh B, 13.5 months).

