### Outcomes

#### Primary outcome

The primary outcome will be Time to Progression (TTP), defined as the time elapsed since the start of treatment until the determination of progressive disease. Progressive disease will be determined by image evaluation according to the modified RECIST (mRECIST) response evaluation criteria [33]. The mRECIST overall response assessment includes the evaluation of target lesions response, non-target lesions response and the occurrence of new lesions.

The baseline for calculation of TTP will be the date of minimization. Imaging data will be assessed by independent radiologists. In case progressive disease is determined during follow-up, patients have reached the study endpoint and will be treated according to best medical practice. Patients who switch to other treatments are registered as such and overall survival will be monitored.

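### The sample size allows for 2% loss to follow-up but not for death before progression, which removes further events from a calculation already far short of its stated power

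*Protocol article*

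**What the plan says.** The Sample size calculation section of the protocol article sizes the trial "using the log rank test" and starts from these inputs: "Assuming a follow-up time of 24 months and a median time to progression of 13.3 months" in the radioembolization arm. The target is a 20% difference (2.7 months), "with a power of 90% and a two-sided Alpha Risk of 5" per cent, and it concludes that "70 patients in each treatment arm will be required". It then makes one allowance for attrition: "Taking a hypothetical loss to follow-up of 2% into account in both treatment arms, based on earlier experience with this patient group". With that allowance, power is given as 80% at the same 70 per arm. Death is not mentioned.

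The Primary outcome section has TTP "defined as the time elapsed since the start of treatment until the determination of progressive disease", judged on imaging by mRECIST. Death is not an event.

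The Background section on radioembolization describes the cohort that supplied the 13.3-month median. In its intermediate-stage patients "median survival was 17.2 months (Child-Pugh A, 17.3 months and Child-Pugh B, 13.5 months"; the matching TTP medians are 13.3 months overall, 13.3 in Child-Pugh A and 17.4 in Child-Pugh B. The TACE section cites survival of about 17 months. Child-Pugh B patients are eligible under Study participants.

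**The concern.** Log-rank power depends on the number of progressions observed. A patient who dies unprogressed leaves the risk set without adding one, just as a patient lost to follow-up does. The calculation counts the second kind of exit and omits the first. Yet the study it draws on has a median survival only about four months longer than its median TTP, and in one eligible subgroup survival is the shorter of the two.

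If pre-progression deaths are common, 70 per arm will yield fewer events than the calculation supposes. A non-significant result could then be read as evidence that the treatments are equivalent when the trial had little chance of separating them. The omission also matters for any correction: a new calculation that repaired only the effect size and kept 2% attrition would still overstate the events per patient enrolled.

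**Working it through.** **Inputs.** From the Sample size calculation: 70 per arm, 24 months, TTP median 13.3 months for radioembolization, difference 2.7 months, two-sided 5%. The direction is not stated, so TACE is 10.6 or 16.0 months. From the Background: median survival 17.2 months (Child-Pugh B 13.5, with TTP 17.4). Assumptions: exponential times and a full 24 months of observation for every patient, which is the favourable reading.

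**Step 1. The plan's own figure.** Required events = 4(1.960 + 1.282)²/(ln HR)².
- TACE 10.6: HR = 10.6/13.3 = 0.797, so 817 events for 90% power (610 for 80%). About 75% progress by 24 months, so N is about 1,085.
- TACE 16.0: HR = 13.3/16.0 = 0.831, so 1,231 events; about 68% progress, so N is about 1,810.

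The printed 140 is not reproduced. With no deaths and no loss, 140 patients give 105 (or 95) events. Power = Φ(|ln HR|·√events/2 − 1.96):
- TACE 10.6: Φ(0.2269·√105.4/2 − 1.96) = 21%.
- TACE 16.0: Φ(0.1848·√95.2/2 − 1.96) = 15%.

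Seventy per arm reaches 90% only for HR of about 0.54 (13.3 vs 7.2 months) or 0.49 (13.3 vs 27.3), neither of which the article states.

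**Step 2. Do the quoted medians imply deaths before progression?** If nobody died unprogressed, each patient's survival would be at least as long as the TTP, and median survival could not be the shorter. In Child-Pugh B it is. Even if death followed progression at once, the pre-progression death hazard would be ln2/13.5 − ln2/17.4 = 0.0513 − 0.0398 = 0.0115 per month. That is 22% of the overall hazard, and the share dying unprogressed by 24 months is 0.224 × (1 − exp(−24 × 0.0513)) = 16%.

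The overall medians (17.2 vs 13.3) do not force a figure. Fitting them with a death hazard that differs before and after progression gives 39% dying unprogressed in the radioembolization arm if the hazards are equal, 28% if the hazard is three times higher after progression, and 16% if ten times higher.

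**Step 3. Events after deaths.** Let the pre-progression death hazard be ld = f·ln2/17.2 (ln2/17.2 = 0.0403 per month) and the progression hazard lp = ln2/median. Events per arm = 70·lp/(lp+ld)·(1 − exp(−24(lp+ld))). Deaths without progression use ld in the numerator and no factor of 70. The fraction f is assumed.

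| f | TACE 10.6: events | dying unprogressed, by arm | power at 2.7 months | TACE 16.0: events | power at 2.7 months |
|---|---|---|---|---|---|
| 0 | 105 | 0 | 21% | 95 | 15% |
| 0.25 | 96 | 11-13% | 20% | 87 | 14% |
| 0.5 | 88 | 21-23% | 19% | 79 | 13% |
| 0.75 | 81 | 28-32% | 17% | 72 | 12% |
| 1 | 75 | 35-39% | 16% | 67 | 11% |

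With TACE at 16.0 months the shares dying unprogressed are slightly higher, up to about 42% in that arm at f = 1.

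**Step 4. The proportional effect.** If r is the ratio of events with and without deaths, a design that truly had 90% power keeps Φ((1.960 + 1.282)√r − 1.960). For TACE 10.6, r = 0.913, 0.837, 0.771 and 0.712, giving 87%, 84%, 81% and 78%. For TACE 16.0 the last is 77%. A true 80% would fall to about 65-76%. By comparison, a 2% loss alone leaves 89.4% if 2% of events vanish outright, or 89.8% if the loss is spread evenly over 24 months.

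**The case against.** The strongest reply is that deaths are a minor part of the problem. A reader might infer that omitted deaths are why the 90% and 80% are not delivered. The article's own inputs do not support that: at the printed effect, power is 21% (or 15%) with no deaths at all, and deaths take off only 1 to 5 points. A reader might equally infer that the trial, once corrected, has 77-87% power for a 2.7-month difference. It does not; those figures belong to some larger effect that the article does not state. Both parts of this objection stand.

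It is also true that f is not in the document. Overall survival includes deaths after progression, so the 62% dead by month 24 under an exponential median of 17.2 months does not measure deaths before progression. The Child-Pugh B medians are subgroup estimates quoted without sizes or intervals, the share of such patients in this trial is unknown, and its exclusions (for example, life expectancy under three months) may lower early mortality. These points make the result a range. They do not bring it near 2%: the Child-Pugh B lower bound is already about 16%, and the overall medians give 16% even when death is ten times as likely after progression. Only near-immediate death after progression in all other patients would bring the overall figure close to the allowance.

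Finally, the 2% has no time unit. If it meant 2% per month, it would be of the same order as the death hazard at f = 0.5 (0.020 per month). Nothing in the text says so, it is described as loss to follow-up, and even that reading would bring 90% down only to about 84%, not the printed 80%. The mismatch between a 2% loss and a 10-point drop in power is a separate inconsistency.

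**Conclusion.** The point holds as an added loss of events. The calculation allows for 2% attrition, while the cohort it relies on points to roughly 11-39% dying unprogressed by 24 months (TACE at 10.6 months, f from 0.25 to 1). Expected progressions are about 75-96 instead of 105, or 67-87 instead of 95 with TACE at 16.0 months: a loss of about 9-30%. Power at the printed difference falls from about 21% to 16-20%, or from 15% to 11-14%.

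The result rests on exponential times, 24 months for every patient, the source cohort's mortality carrying over to both arms, and the assumed f. That deaths before progression exceed 2% is secure in Child-Pugh B if the quoted medians are taken at face value; for the whole population it is probable, and its size is uncertain. The main failure of the stated power lies in the effect size and the number of patients, and a death allowance alone would not repair it.

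**What to change.** In the Sample size calculation section:

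1. Replace the 2% input with total censoring before progression, meaning loss to follow-up plus death without progression, based on the survival figures of the same cohort, and give the time unit.
2. State the hazard ratio and its direction.
3. State the expected number of progressions at 24 months. With the figures here that is about 75-96 for 13.3 vs 10.6 months, or 67-87 for 13.3 vs 16.0.
4. Restate the power of 70 per arm at that hazard ratio as a range over the pre-progression death hazard. If the 2.7-month difference is kept, the range is about 16-20% or 11-14%; the 77-87% range must not be attached to it.

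The cost is one rerun of the calculation and a few revised sentences. Enrolment need not change to make this correction; the price is a much less favourable stated power.

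### A 2% loss to follow-up cannot take power from 90% to 80% at 70 per arm, so the stated power figures cannot both be right

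*Protocol article*

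**What the plan says.** All the figures are in the protocol article, under Outcomes, Sample size calculation.

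- Size: "A total of 140 patients will be included".
- Assumptions for the log-rank calculation: "Assuming a follow-up time of 24 months and a median time to progression of 13.3 months after" radioembolization, and "a clinically relevant effect size of 20% difference in time to progression (2.7 months").
- First power statement: "with a power of 90% and a two-sided Alpha Risk of 5%, 70 patients in each treatment arm will be required".
- Second power statement: "Taking a hypothetical loss to follow-up of 2% into account in both treatment arms", the design "still gives a power of 80% if 70 patients per treatment arm are included (Alpha Risk remains 5"%).

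The loss of 2% is given without a time unit.

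**The concern.** The second power statement repeats the first with one change, the 2% loss. A loss that small should move power by less than one percentage point, yet the stated power drops by ten. The error therefore lies in the 90%, the 80% or the 2%, and the text does not show which.

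Time to progression by log-rank test is the primary analysis, and this paragraph is where the article justifies 140 patients. A reader of a null result would take it to come from a trial that kept 80% power for a 20% difference after attrition. If the base figure is also wrong, that reading is badly mistaken.

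**Working it through.** **Inputs, all from the sample size section:** 70 per arm, 1:1; two-sided alpha 5%; power 90% before loss and 80% after; loss 2% in both arms; 24 months of follow-up; median 13.3 months after radioembolization; difference 2.7 months (20% of 13.3 is 2.66).

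**Step 1. Does 2% loss take 90% to 80%?** With d events in two equal arms, log-rank power is approximately Φ(|ln HR| × √d / 2 − 1.960). The hazard ratio and the events enter only through the product |ln HR| × √d / 2. If power is 90%, that product is 1.960 + 1.282 = 3.242, whatever the hazard ratio. Losing a share f of the events multiplies it by √(1 − f):

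| Share of events lost | 3.242 × √(1 − f) | Power |
|---|---|---|
| 2% | 3.209 | 89.4% |
| 5% | 3.159 | 88.5% |
| 10% | 3.075 | 86.8% |
| 25% | 2.807 | 80.2% |

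Power of 80% needs a product of 1.960 + 0.842 = 2.802. The ratio of information is (2.802 / 3.242)² = 0.747, so 25.3% of the events would have to be lost. Against the stated 2% that is 25.3 / 2, or about 12 to 13 times as much. In the other direction, if 80% after a 2% loss is right, power before loss is Φ(2.802 / √0.98 − 1.960) = 80.8%, not 90%.

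**Step 2. Could the 2% be a rate per period?** This step assumes exponential progression and exponential loss over 24 months. The chance of an observed event is λ / (λ + γ) × (1 − exp(−(λ + γ) × 24)), where λ = ln 2 / median and γ is the loss hazard. The comparator median is set so that power without loss is exactly 90%, which takes 7.2 months (shorter) or 27.2 months (longer).

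| 2% read as | Power, shorter comparator | Power, longer comparator |
|---|---|---|
| total over 24 months | 89.8% | 89.8% |
| per year | 89.6% | 89.5% |
| per 3 months | 88.3% | 88.0% |
| per month (1 − 0.98²⁴ = 38% lost in all) | 84.7% | 83.7% |

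No reading reaches 80% within the stated follow-up.

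**Step 3. Is the 90% itself right?** The 2.7-month difference puts the comparator median at 13.3 − 2.7 = 10.6 or 13.3 + 2.7 = 16.0 months. Take exponential times and 24 months of follow-up for every patient, so the chance of progression is 1 − 0.5^(24 / median): 0.714 at 13.3 months, 0.792 at 10.6 and 0.646 at 16.0.

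- **13.3 v 10.6:** d = 70 × (0.714 + 0.792) ≈ 105. |ln(10.6 / 13.3)| = 0.227. Power = Φ(0.227 × √105.4 / 2 − 1.960) = Φ(−0.795) = 21.3%, or 21.0% with 2% fewer events.
- **13.3 v 16.0:** d = 70 × (0.714 + 0.646) ≈ 95. |ln(16.0 / 13.3)| = 0.185. Power = Φ(0.185 × √95.2 / 2 − 1.960) = Φ(−1.058) = 14.5%, or 14.3% with 2% fewer events.
- **If all 140 patients progressed:** 26.8% and 19.3%.
- **Events needed for 90% power,** 4 × 3.242² / (ln HR)²: about 817 and 1,231, against 140 patients.

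The plan's 90% is therefore not reproduced. Reading the 20% as a difference of 20 percentage points in the proportion free of progression does not give 70 per arm either: the variants tried need 57 to 129 per arm for 90% power.

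**The case against.** Four points can be made for the text.

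1. **The 80% may be a floor.** The word *still* could mean that the trial stays above the usual 80% threshold, and 89.4% does. On that reading neither power figure is strictly false. But the sentence gives 80% as the power, and if a floor was meant, the power after loss goes unreported. The sentence needs correcting either way.
2. **The loss has no time unit.** This is true, and the multiple of about 12 assumes that 2% is the total. A rate of 2% per month narrows the gap to about 4 to 5 points. It would come near 80% (79.5% to 82.3% by the Step 2 formula) only if every patient were followed for 48 months, and the plan states 24.
3. **2% of patients is not exactly 2% of events.** If all 2.8 lost patients (2% of 140) would have progressed, 2.8 / 105 = 2.7% of events go and power is 89.2%. Letting the lost patients also dilute the effect gives 88.2%. Both remain far from 80%.
4. **Taken alone, the inconsistency understates power.** If the 90% were right, the power after loss would rise from 80% to about 89%, and the loss sentence does not change the 70 per arm. This is fair: the unfavourable consequence comes from Step 3, not from the 2% sentence. But Step 3 uses the paragraph's own inputs and shows that the 90% cannot be trusted, so the mismatch cannot be settled by keeping the 90%.

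A condensed article may leave detail to the full protocol. That excuses omissions, not figures that disagree with one another.

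**Conclusion.** The concern holds. At 70 per arm and unchanged alpha, 90% power becomes about 89.4% after a 2% loss, which is 9.4 points above the stated 80%. The stated drop needs about 25% of the events to be lost. This result rests only on the usual normal approximation for the log-rank test and on reading 2% as a total. It needs no hazard ratio, median or accrual pattern, and a monthly reading still leaves about 84% to 85%.

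In addition, neither power figure follows from the stated effect, which gives about 14% to 21% power. That part assumes exponential progression times, 24 months of follow-up for all patients, and the 20% read as a difference in medians, as the 2.7 months in the text indicates. The paragraph must be corrected because it attributes to the design a power that its own inputs do not support.

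**What to change.** Recompute and restate the paragraph so that it gives:

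- the base power at 70 per arm for the 2.7-month difference, with the comparator median and its direction stated;
- the loss to follow-up with its time unit;
- the power after that loss, which for a 2% total differs from the base by less than one point.

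If the 80% was meant to allow for about 25% loss of information, state that loss in place of 2%. If the original calculation used a different effect from the one printed, state the effect that was used.

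The cost is a corrected passage of a sentence or two. No change in enrolment is proposed. The stated power will become less favourable. The Trial status section reports ten patients allocated and treated, with results pending, so the correction can be made well before the analysis.
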